### Exclusion criteria

2.4

Participants who meet the preliminary screening criteria will be excluded if any of the following conditions are present:Structural lesions are present in the affected shoulder, including fracture, dislocation, any partial-thickness or full-thickness rotator cuff tear, marked shoulder osteoarthritis, or a history of major surgery on the affected shoulder that could explain the current symptoms;Shoulder pain or shoulder dysfunction is caused by other definite etiologies, including subacromial impingement syndrome, calcific tendinitis, cervicogenic shoulder pain, radiculopathy, bone tumor, shoulder tuberculosis, infectious arthritis, or inflammatory arthropathy;Bilateral shoulder pain or marked bilateral restriction of shoulder movement is present, and the main affected side cannot be clearly determined. Participants will also be excluded if bilateral symptoms may affect outcome assessment;They have participated in another clinical trial within the previous month, or have received treatments within the previous 3 months that may substantially affect the evaluation of pain or shoulder function. These treatments include intra-articular shoulder injection, subacromial bursa injection, tendon sheath injection, nerve block, hydrodilatation, acupotomy, miniscalpel-needle therapy, or other interventional treatments;They have received acupuncture, EA, tuina, physical therapy, intensive rehabilitation training, or other treatments that may substantially affect the evaluation of shoulder pain or shoulder ROM within 2 weeks before screening;They have contraindications to acupuncture or EA, including rash, ulceration, or infection at the needling site; coagulation disorders or a high risk of bleeding; current anticoagulant use judged by the study physician to be unsuitable for acupuncture; a cardiac pacemaker or other implanted electronic device; or severe metal allergy to acupuncture needles;They have severe diseases of the heart, brain, liver, kidney, hematopoietic system, or other major systems. They will also be excluded if they have an active infectious disease, severe skin disease, or any condition judged by clinical assessment to make them unsuitable for the study intervention;They are pregnant, lactating, or planning pregnancy during the study period;They have a severe mental disorder, marked cognitive impairment, or language communication disorder that prevents them from understanding the study procedures or completing outcome assessments;They are expected to be unable to complete the treatment or follow-up assessments because of personal plans, relocation, work arrangements, or other practical reasons.

### Recruitment process

2.5

Participants will be mainly recruited from the outpatient acupuncture clinic of the Third Clinical Hospital Affiliated to Changchun University of Chinese Medicine. The research team will consecutively screen potentially eligible patients attending the outpatient clinic. Recruitment information will also be released through hospital posters, the official hospital website, and the hospital WeChat public account. All recruitment materials will be approved by the ethics committee before use. These materials will include the study purpose, main eligibility criteria, trial procedures, potential benefits and risks, contact information, and participants’ rights.

Individuals interested in participating will first undergo pre-screening. Pre-screening may be conducted face to face, by telephone, or online. It will mainly assess age, main symptoms, disease duration, previous treatment history, and obvious exclusion factors. Individuals who are potentially eligible after pre-screening will be scheduled for a formal screening visit at the research clinic. Formal screening will be performed by trained research staff and study physicians and will include medical history taking, a standardized physical examination, preliminary assessment of shoulder ROM, standard shoulder radiography, and mandatory diagnostic ultrasonography of the affected shoulder. Ultrasonography will be performed by trained imaging personnel and will assess the integrity of the supraspinatus, infraspinatus, subscapularis, and teres minor tendons, as well as other relevant periarticular soft-tissue structures. Shoulder MRI will be obtained if the ultrasonographic findings are inconclusive or if another structural lesion is suspected. All imaging findings will be reviewed before eligibility is confirmed and randomization is performed. Final eligibility will be determined according to the diagnostic criteria in Section 2.2, the inclusion criteria in Section 2.3, and the exclusion criteria in Section 2.4. A screening log will be maintained. Screening results and reasons for non-enrollment will be recorded for all screened individuals.

Before any study-related procedure is performed, research staff will provide full information to each candidate participant. This information will include the study purpose, trial procedures, potential benefits and risks, alternative treatment options, data confidentiality measures, the right to withdraw, and protection of medical rights after withdrawal. Candidate participants will be given sufficient time to ask questions and consider participation. Individuals who voluntarily agree to participate will sign written informed consent and receive a unique study identification number. Participants who have signed informed consent and are confirmed as eligible will complete the baseline assessment before randomization. At the baseline visit and before randomization, the study physician will re-evaluate the participant’s current clinical stage. Pain-dominant status will be reconfirmed on the basis of the predominant clinical complaint and the presence and intensity of resting and nocturnal pain. Candidates whose symptoms have transitioned to a stiffness-dominant presentation or who no longer meet the pain-dominant criteria will not be randomized, and the reason for non-enrollment will be recorded in the screening log. Personal information will be used only for the purposes of this study and will be managed in a de-identified manner. Participants may withdraw from the study at any time without penalty. Reasons for withdrawal will be recorded in the screening, enrollment, and follow-up records when available.

### Sample size calculation

2.6

The sample size was calculated using PASS version 2023. Although the primary analysis will use an analysis of covariance model with adjustment for baseline VAS, the sample size was conservatively estimated using a two-sided test for comparing the means of two independent groups, without assuming any efficiency gain from baseline adjustment.

A published randomized controlled trial involving patients with frozen shoulder reported a post-treatment standard deviation of approximately 1.9 cm for the 10-cm VAS in both active treatment groups (12). On this basis, the common standard deviation was conservatively set at 2.0 cm. Considering that the present trial compares two active EA frequency regimens, the smallest between-group difference of interest was set at 1.0 cm, corresponding to a standardized effect size of 0.50. This target between-group mean difference is distinct from the individual-level minimal clinically important difference, which reflects the magnitude of change perceived as beneficial by an individual participant. With a two-sided significance level of 0.05, statistical power of 0.80, and a 1:1 allocation ratio, 64 participants with evaluable primary-outcome data will be required in each group. Allowing for an anticipated attrition rate of 15%, 76 participants will be recruited per group. Therefore, the total planned sample size will be 152 participants.

### Randomization and allocation concealment

2.7

Participants who meet the inclusion criteria, meet none of the exclusion criteria, and provide written informed consent will be randomized after the baseline assessment. They will be assigned in a 1:1 ratio to the low-frequency EA group (2 Hz) or the high-frequency EA group (100 Hz). The randomization sequence will be generated by an independent statistician using a computer-generated method. The statistician will not participate in participant recruitment, treatment, outcome assessment, or data analysis. Block randomization will be used. The block size will be determined and kept confidential by the independent statistician.

Allocation concealment will be implemented through a central randomization system. Randomization will be performed only after eligibility confirmation, informed consent, and baseline assessment have been completed. The allocation result will be available only to the treating acupuncturist responsible for delivering the intervention. The treating acupuncturist will not participate in outcome assessment or data analysis. Investigators, outcome assessors, data managers, and statistical analysts will have no access to the randomization sequence or the complete allocation list before database locking. The randomization sequence, allocation records, and system operation logs will be stored by independent personnel.

### Blinding

2.8

This trial will use a participant- and outcome assessor-blinded design. Participants will be informed that the trial compares two EA frequency regimens that have been used in clinical practice. They will not be informed of their group allocation. The two groups will be kept consistent in acupoint selection, needles, treatment position, needle retention time, treatment setting, treatment procedures, and communication scripts. These measures will be used to minimize expectation bias.

EA produces perceptible sensations, including soreness, numbness, distension, heaviness, tingling, and slight local muscle twitching. Because different stimulation frequencies may produce different temporal sensations, complete participant blinding cannot be guaranteed. Participants will not be informed of the expected sensory characteristics of either frequency. The EA device display and control panel will be positioned outside the participant’s line of sight, and treating acupuncturists will avoid mentioning the selected frequency or describing frequency-specific sensations during treatment.

Treating acupuncturists cannot be blinded because they need to set the EA frequency. Therefore, they will not participate in participant screening, outcome assessment, data entry, data management, or statistical analysis.

Outcome assessors, data managers, and statistical analysts will remain blinded throughout the trial. During data entry and statistical analysis, the groups will be coded as group A and group B. The specific EA frequency corresponding to each code will not be revealed before database locking. All research personnel will receive standardized training before the trial begins and will follow standard operating procedures (SOPs) for blinded communication, treatment arrangements, outcome assessment, and data management. Before participant recruitment begins, a formal role-assignment and delegation log will be established to define the responsibilities of personnel involved in participant screening, eligibility assessment, intervention delivery, outcome assessment, data entry, data management, and statistical analysis. These roles will be assigned to different personnel wherever blinding requires separation. Treating acupuncturists will have access only to participant information and treatment parameters necessary for intervention delivery and will not have access to outcome-assessment data or the blinded analysis dataset. Treatment delivery and outcome assessment will be scheduled and conducted separately, and standardized communication scripts will be used in both treatment groups. Any event that may lead to unblinding will be recorded promptly. The record will include the time, reason, personnel involved, and management measures.

The success of participant blinding will be assessed at T1, at the end of treatment 2 weeks after treatment initiation. Participants will be asked whether they believe they received the 2 Hz regimen, the 100 Hz regimen, or are uncertain about their allocation. The reason for their judgment and their level of confidence on a 0–10 scale will also be recorded. Participants’ guesses will be cross-tabulated with their actual treatment allocation, and the proportions of correct, incorrect, and uncertain responses will be reported. If necessary, outcome assessors may also be surveyed to evaluate the success of assessor blinding. The participant blinding results, including the reasons for participants’ judgments and their confidence ratings, will be considered when interpreting the trial findings.

Safety will be monitored continuously throughout the trial. Emergency individual unblinding may be performed if a serious adverse event, marked disease aggravation, or another condition requiring urgent medical management based on group allocation occurs. Emergency unblinding must be requested by the investigator with a clear explanation of medical necessity and confirmed by the principal investigator or the trial steering committee. The participant’s actual group allocation will then be obtained through the central randomization system. Emergency unblinding will be limited to the relevant participant and will not affect the blinding of other participants or research personnel. All emergency unblinding events will be documented. The record will include the time of unblinding, reason, decision-making process, personnel involved, and subsequent management. The case report form and adverse event records will be updated accordingly.

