### Patient and public involvement, trial oversight, monitoring, and open science

2.14

No patient or public representatives were involved in the initial design of this trial protocol. Participant feedback collected during recruitment, treatment, and follow-up will be considered when refining future multicenter studies or optimizing the acceptability of the intervention procedures.

Changchun University of Chinese Medicine is listed as the applicant institution, and the Third Clinical Hospital Affiliated to Changchun University of Chinese Medicine will serve as the clinical study site and coordinating center for this single-center trial. Trial-related administrative matters will be coordinated by the study site and the principal investigator. The principal investigator, [name], will oversee the overall conduct of the trial. The coordinating center will be responsible for participant recruitment, intervention delivery, outcome assessment, safety management, data collection, and document storage. The data management team and independent statistician will be responsible for eCRF development, data checking, database locking, and statistical analysis. The funder will have no role in study design, trial conduct, data collection, data management, statistical analysis, interpretation of results, manuscript preparation, or the decision to submit the manuscript for publication.

A formal independent data monitoring committee will not be established because this is a single-center, low-risk, non-drug trial with a short treatment period. Safety and trial conduct will be reviewed by the principal investigator and the study team at regular quality-control meetings. No interim efficacy analysis is planned. The study may be temporarily suspended or terminated early in the event of unexpected safety concerns, serious protocol noncompliance, severe recruitment difficulty, or a decision by the ethics committee or study institution.

Important protocol amendments will be submitted to the ethics committee for approval before implementation and updated in the trial registry when applicable. Relevant amendments will be communicated to investigators, outcome assessors, data managers, and other trial personnel. If an amendment affects participant rights, safety, or study procedures, the informed consent form and other participant-facing materials will be revised accordingly.

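### With one shared A/B label per arm from data entry onward, a single emergency unblinding can reveal both arms to anyone who also sees the labels

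*Protocol article*

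**What the plan says.** Four statements in Sections 2.7 and 2.8 of the protocol article bear on this point.

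- Access to allocation (Section 2.7): "Investigators, outcome assessors, data managers, and statistical analysts will have no access to the randomization sequence or the complete allocation list before database locking".
- Coding (Section 2.8): "During data entry and statistical analysis, the groups will be coded as group A and group B". On the key to the codes: "The specific EA frequency corresponding to each code will not be revealed before database locking". On who stays blinded: "Outcome assessors, data managers, and statistical analysts will remain blinded throughout the trial".
- Emergency unblinding (Section 2.8): the investigator requests it, and the request is "confirmed by the principal investigator or the trial steering committee". The participant's "actual group allocation will then be obtained through the central randomization system". The event is documented, and the case report form and adverse-event records are then updated.
- Stated reach of such an unblinding (Section 2.8): "Emergency unblinding will be limited to the relevant participant and will not affect the blinding of other participants or research personnel".

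Section 2.12 adds that the eCRF covers randomization, intervention delivery, outcomes and adverse events, and that the data manager checks it. Section 2.14 sets up no independent monitoring committee and says: "Safety and trial conduct will be reviewed by the principal investigator and the study team at regular quality-control meetings".

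**The concern.** The assurance about unblinding is given without conditions, but the coding rule a few lines earlier does not support it. A code shared by a whole arm protects the blind only while nobody who sees the labels knows any one participant's frequency. Emergency unblinding produces exactly that piece of knowledge before lock. The labels at data entry also fit poorly with Section 2.7: a list of study IDs marked A or B is the complete allocation list apart from a single two-way key.

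Several judgements remain open until lock: data queries (Section 2.12), the causality of adverse events (Section 2.11.3), and which deviations are major and whose adherence is acceptable (Section 2.13). The last of these decide the per-protocol set and some sensitivity analyses. With no independent committee, the trial's own team makes these judgements. If a member of that team can decode the arms, the decisions are no longer blinded, although the text says that they are.

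**Working it through.** **The figure used.** The only number involved is the planned total. Section 2.6 gives SD 2.0 cm, difference 1.0 cm, two-sided alpha 0.05, power 0.80, 1:1 allocation and 15% attrition. A two-sample t-test with standardized effect 1.0/2.0 = 0.50 needs 63.77, so 64 per group (power 0.801 at 64). Then 64/0.85 = 75.3, so 76 per group, and 2 × 76 = 152. The plan's figure is reproduced, and nothing below alters it.

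**What one unblinding reveals.** This step is logic, not estimation.

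1. With labels A and B there are two possible keys: A = 2 Hz and B = 100 Hz, or the reverse.
2. Suppose a person sees the labels of m participants, including the unblinded one, and learns that participant's frequency. One of the two keys is ruled out, and the other gives the frequency of all m.
3. The number decoded therefore depends on what that person sees:
   - shared labels visible for m participants: m decoded. For example, 38 if 38 have been entered, 76 if 76 have been entered, and 152 if all have been entered and all are visible;
   - labels not visible: 1;
   - participant-specific codes: 1.

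The statement that an unblinding stays with one participant is true in the last two cases and false in the first.

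**Which case the text describes.** Setting the statements side by side:

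- Section 2.8 has the labels in use during data entry, so they exist before lock. It does not say who sees them.
- Section 2.7 withholds the complete allocation list from investigators, assessors, data managers and analysts, but does not say how that fits with labels at data entry.
- Section 2.8 says that the allocation is obtained from the randomization system, but names no recipient.
- The record of the event comprises time, reason, decision process, personnel and later management. The allocation is not among these items. The case report form is nevertheless updated, with no instruction to leave the frequency out, and data managers check that form.
- Nothing says that codes are unique to a participant, or that a person who learns an allocation is kept away from coded data.

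The text therefore does not place the trial in a case where the assurance holds.

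**The case against.** The strongest reply is that decoding needs two things to meet in one person, the labels and a revealed frequency, and the article states neither for anyone in particular. A reader might infer that one unblinding hands the principal investigator and the data staff all 152 allocations. The documents do not support that. They do not say that the principal investigator sees A/B labels. Confirming a request is not the same as receiving the answer, and a steering committee may confirm instead. Nor do they say that the frequency is entered in the case report form. The roles listed as remaining blinded do not include the principal investigator, so it is not shown that emergency unblinding is what would break that person's blind. All of this stands, and it limits the point to a property that is not secured.

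A reader might also infer that a breach would go unreported. Section 2.12 points the other way: events that may compromise blinding are documented with their possible effect, classed as protocol deviations, and considered in sensitivity analyses and interpretation. That safeguard is real, but it acts after the breach. The coding could prevent it.

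The consequences are also limited. The primary outcome is a VAS marked by the participant and analysed by ANCOVA on the full analysis set. The per-protocol set serves sensitivity analysis only. Treating acupuncturists know the allocation in any case. No route to participants or outcome assessors is shown.

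Finally, the location of labels in the data system could be seen as a matter for the SOPs. This carries less weight: the coding rule and the assurance are both stated in the article, they do not fit together, and Section 2.14 describes the article as the full protocol.

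**Conclusion.** The point holds in a limited form. Because each arm has one label from data entry onward, an emergency unblinding before lock can reveal both arms to anyone who also sees the labels, including that of the unblinded participant. The reach is every participant whose label that person sees: those entered so far, at most 152, and only 1 where labels are not visible. The unconditional assurance in Section 2.8 is therefore not secured, and the bar on the complete list in Section 2.7 is not reconciled with labels at data entry.

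The conclusion assumes that A and B are shared arm codes, as the text reads, and that at least one emergency unblinding occurs before lock. The article gives no rate. The intervention is described as low-risk, so such events may be rare, but one is enough. The effect on the primary VAS comparison is likely small, and sample size, alpha and power are unaffected. What is exposed is data queries, adverse-event review, and deviation and per-protocol decisions. Section 2.14 does not describe the steering committee named in Section 2.8. That is a side issue, and the point does not rest on it.

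**What to change.** In Section 2.8, take data entry out of the sentence on A/B coding, so that the working eCRF identifies participants by study ID only. Have the independent personnel who hold the randomization records release the A/B list to the analyst at database lock. Participant-specific codes before lock would serve the same purpose.

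In the emergency-unblinding paragraph, state that the case report form and adverse-event records note only that unblinding occurred, with date and reason, and that the revealed allocation stays in a restricted log outside the data staff's view. Add to Section 2.7 that the bar on the complete allocation list covers arm-labelled lists before lock.

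None of this changes when an unblinding may be requested. The cost is protocol and SOP wording and the removal of the arm label from the working eCRF, with no extra staff. The small downside is that no arm-coded listings are available before lock.
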